#### Randomization

A cluster-randomized design is used, which means that randomization to either the intervention or control condition takes place at the GPC level, and that all participants in a GPC are assigned to the same condition. Neither GPCs nor participants are blinded to their assigned condition during the trial. However, during recruitment, both GPCs and the researcher are unaware of the randomization outcome to ensure that participation is not influenced by assigned conditions. The randomization outcome will be defined by a computer-generated randomization list using simple randomization (1:1), which was generated before the start of recruitment and stored with a third person.

### Statistical Methods

#### Overview

The first 2 steps of the analysis will test for statistical differences at baseline in lifestyle behaviors, QoL, demographics, and psychosocial and medical symptoms between the 2 study groups. Blinding of the analyst will be applied for primary outcomes. Patterns and mechanisms of missing data will be explored. Thereby, special attention will be paid to dropouts. Randomization of the GPCs should account for an even distribution between the experimental and control conditions of socioeconomic factors or other confounding factors that may skew our results. However, in case conditions are unbalanced, these factors will be adjusted for in the analysis. If necessary, other statistical adjustment procedures will be applied to minimize the impact of any bias.

Multilevel linear regression analyses will be conducted to test for differences in residual change scores between the intervention and control groups on the primary and secondary outcomes at the 6-month follow-up and the 6- and 12-month follow-up combined. Intention-to-treat (ITT) analyses with multiple imputations will be applied. Participants will be nested within GPCs to account for potential interdependence between participants. Multilevel linear regression analyses with a random intercept for GPC level will be performed to account for possible interdependence in the effect analyses. The effects on the population will be assessed via CIs.

The primary outcome measures will be the residual change scores in lifestyle behaviors, but also differences in the secondary outcomes (anxiety and depression, fatigue, [health-related] QoL, and health-related costs). Blood pressure at 6 months will be compared between the intervention and control groups. In addition, moderation analyses will be conducted to examine different potential moderators such as age, gender, type of treatment, and level of education [8-11]. Subanalyses may be performed to explore individual differences that may be attributed to the degree of participation in the intervention. Besides factors on the level of participants, factors on the level of GPCs will be considered for further analysis. Finally, process evaluation data will be analyzed and summarized descriptively.

In addition, Bayes factor analyses will complement the primary analysis of the effects of the blended CAG intervention on the primary and secondary outcomes. A Bayes factor analysis expresses the relative strength of the evidence supporting competing hypotheses. This study examines support for the hypothesis that the blended CAG intervention has greater effects than care as usual as opposed to support for the hypothesis that the conditions do not differ or that the blended CAG intervention has a smaller effect than care as usual. In addition, the strength of support for the hypothesis that the blended CAG intervention has no smaller effects than care as usual will be compared to the support for the hypothesis that the blended CAG intervention has smaller effects than the effects found in the online-only CAG intervention, as studied in previous research [8-11]. In principle, default prior distributions will be used. It will be verified that these prior distributions are sufficiently diffuse, do not overwhelm the data, and do not destabilize the analysis.

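### Covariate adjustment is triggered by observed baseline imbalance instead of a fixed prognostic set, so moderate chance imbalances would mostly go unadjusted

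*Protocol article*

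**What the plan says.** In the protocol article, Statistical Methods, Overview, the analysis opens with steps that "will test for statistical differences at baseline in lifestyle behaviors, QoL, demographics, and psychosocial and medical symptoms between the 2 study groups". The same paragraph expects allocation to deliver balance ("Randomization of the GPCs should account for an even distribution between the experimental and control conditions of socioeconomic factors") and then provides for the case where it does not: "in case conditions are unbalanced, these factors will be adjusted for in the analysis". A further sentence leaves the method open: "If necessary, other statistical adjustment procedures will be applied to minimize the impact of any bias". No covariate is named for the effect models, and no criterion for imbalance is given apart from the tests.

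Two other statements in that section bear on the point. The effect models "test for differences in residual change scores between the intervention and control groups", so each outcome's own baseline is used in every model. And "Blinding of the analyst will be applied for primary outcomes".

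On allocation, the Randomization section says that "randomization to either the intervention or control condition takes place at the GPC level", from "a computer-generated randomization list using simple randomization (1:1"); it mentions no stratification, blocking or minimisation. Results reports 127 participants in 26 practices; Sample Size had aimed for 376 participants in about 40.

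**The concern.** A baseline test asks whether a difference is larger than chance would produce. Under sound randomisation that is already known to be chance, and the p value says nothing about how strongly the factor predicts outcome. Choosing covariates this way can leave out a strong predictor whose imbalance falls short of significance and bring in a factor that is irrelevant but happened to differ. It also leaves the content of the effect models undecided until the baseline data have been compared by arm.

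What is at stake is mainly precision. Across repeated randomisations chance imbalance averages to zero, but in the one trial that is run, an unadjusted imbalance in a prognostic factor displaces the estimate. This trial has fewer practices and participants than planned, so such displacements are larger than the design foresaw.

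**Working it through.** **Inputs from the article.** N = 127 and 26 practices (Results); ICC 0.03, design effect 1.27, effect size 0.30, target of 10 participants per practice (Sample Size); simple 1:1 allocation of practices (Randomization).

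**Assumptions, not in the article.** Two-sided 5% baseline tests that allow for clustering; arms of about equal size; covariate ICC 0.03 (the article's value is for outcomes), with 0 and 0.10 as a range; correlation of a covariate with the outcome, given the outcome's baseline, between 0.2 and 0.5.

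**1. The plan's own figure.** The article attaches no number to the adjustment rule. Its design effect does reproduce: 1 + (10 − 1) × 0.03 = 1.27. The same formula is used below at the cluster size reached.

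**2. What a baseline test can flag.** Mean cluster size is 127/26 = 4.88. Design effect is 1 + (4.88 − 1) × 0.03 = 1.117. The standard error of a standardised baseline difference is √(4 × 1.117/127) = 0.188 SD. The flagging threshold is 1.96 × 0.188 = 0.37 SD.

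**3. Share of chance imbalances missed.** Let D be the realised difference, with mean zero and the standard error above. Flagged imbalances make up 5% of all trials and all lie above the threshold. Below the threshold, the share of imbalances larger than x that are missed is therefore 1 − 0.05/P(|D| > x). At ICC 0.03, P(|D| > x) is 0.286, 0.182 and 0.110 for x = 0.20, 0.25 and 0.30.

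| Setting | Flagged above | Missed, >0.20 SD | >0.25 SD | >0.30 SD | >0.40 SD |
|---|---|---|---|---|---|
| 127 in 26, ICC 0 | 0.35 SD | 81% | 69% | 45% | 0% |
| 127 in 26, ICC 0.03 | 0.37 SD | 83% | 73% | 54% | 0% |
| 127 in 26, ICC 0.10 | 0.41 SD | 85% | 78% | 67% | 10% |
| 376 in 40 (planned), ICC 0.03 | 0.23 SD | 40% | 0% | 0% | 0% |

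Half are missed where P(|D| > x) = 0.10, that is at x = 1.645 × 0.188 = 0.31 SD (0.29 at ICC 0; 0.34 at ICC 0.10).

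For any one covariate, the chance of an unflagged imbalance is 0.286 − 0.05 = 24% above 0.20 SD, 0.182 − 0.05 = 13% above 0.25 SD, and 0.110 − 0.05 = 6% above 0.30 SD.

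**4. Check by simulation.** In 20,000 trials with simple allocation of 26 practices, so uneven arms, and a t critical value on 24 df, the shares missed at ICC 0.03 were 87%, 79% and 66% above 0.20, 0.25 and 0.30 SD. The closed-form figures are, if anything, mild.

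**5. Effect on the estimate.** Shift = correlation × imbalance.

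- Correlation 0.2: 0.2 × 0.20 = 0.04 to 0.2 × 0.30 = 0.06 SD.
- Correlation 0.5: 0.5 × 0.20 = 0.10 to 0.5 × 0.30 = 0.15 SD.

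Against 0.30, these are 13% to 20% and 33% to 50%.

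**6. Precision over repeated trials (same simulation, one covariate).** The SD of the estimated effect with no adjustment, test-then-adjust and fixed adjustment was 0.1917, 0.1899 and 0.1836 at correlation 0.3, and 0.1919, 0.1865 and 0.1669 at 0.5. Test-then-adjust recovers 0.0018/0.0081 = 22% of the available reduction in the first case and 0.0054/0.0250 = 22% in the second.

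**The case against.** Several arguments on the other side have force.

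- **The link from tests to adjustment is inferred.** The article gives no p value cut-off, and sentences on blinding and missing data stand between the tests and the adjustment rule. A reader might infer a p < 0.05 selection rule; the text does not state one, and a separate analysis plan could define imbalance differently. What stands is that adjustment depends on observed imbalance, that the tests are the only comparison described, and that this is a stated rule, not a gap.
- **The strongest covariate is probably already in.** A reader might infer that the outcome's baseline is left to the tests. It is not: residual change scores use it in every model. The relevant correlations for other factors are those that remain after it, which may be weak.
- **Data-driven model choice.** A reader might infer freedom to pick the model that suits the result. The dependence is on baseline data, not outcomes, and the analyst is blinded for primary outcomes. Blinding does not make imbalance a good guide to prognosis.
- **Most imbalances that matter are missed.** The article sets no threshold for what matters. The statement holds below about 0.31 SD and fails above it; at ICC 0.03 everything above 0.40 SD is caught.
- **Low power of the tests.** A reader might calculate that a 0.30 SD difference is flagged only about a third of the time (0.30/0.188 = 1.60; 1 − Φ(1.96 − 1.60) = 0.36). That is power against a population difference. A chance imbalance is simply the one observed: at 0.30 SD it gives p = 0.11 and is never flagged.
- **Uneven numbers of practices.** A split of 10:16 or worse has probability 33%, but it concerns arm size, not covariate imbalance, and adds little to this point.
- **Irrelevant covariates cost little.** With 10 to 20 independent tests (assumed), at least one is flagged by luck in 40% to 64% of trials (1 − 0.95^k), but the price is about a degree of freedom each. The harm lies in what is left out.
- **Baseline comparison has a diagnostic use here.** Under Recruitment of Participants, patients learn their arm in the message that carries the link to the baseline questionnaire, and the article itself raises selection bias, though it considers the effect minimal. This supports looking at baseline differences by arm. It does not support using tests to choose covariates.

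**Conclusion.** The point holds as a moderate weakness in pre-specification. On the natural reading, covariates other than the outcome's baseline enter the models because of observed imbalance, not prognostic value. At the size reached, about 83%, 73% and 54% of chance imbalances above 0.20, 0.25 and 0.30 SD would go unadjusted, and each one moves the estimate by roughly 0.04 to 0.15 SD, depending on how prognostic the factor is.

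These figures rest on a two-sided 5% criterion, a covariate ICC of 0.03, near-equal arms and correlations of 0.2 to 0.5, none of which the article gives for covariates. Comparison with the planned 0.30 also takes both to be on the same SD scale. At correlations near 0.2 the effect is small. The documents do not support a claim that the trial's estimate is biased on average, or that large imbalances would be overlooked.

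**What to change.** Before unblinding, replace the imbalance-triggered rule with a short fixed list of prognostic covariates, used in every effect model whatever balance is observed and alongside the existing adjustment for the outcome's baseline. Candidates already collected at baseline (Outcomes, Overview) are age, sex, education, type of treatment and time since diagnosis. Include the same variables in the multiple imputation model.

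Report baseline characteristics by arm descriptively, without tests, and use that table to look for selection after patients learn their allocation. Show the model without the added covariates as a sensitivity analysis. Delete the open-ended sentence on other adjustment procedures, or label any such analysis exploratory.

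The cost is a few degrees of freedom and no new data. The article places the start of analysis in spring 2025, after data collection, so at its publication the change could still be made in time.

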### Strengths and Limitations

#### Overview

This paper describes the study protocol for an RCT of the effectiveness of a blended care intervention for cancer aftercare in general practice. Conducting an RCT strengthens our interpretation of the results by controlling for confounding through randomization. In addition, the current research is very similar to the previous research evaluating the effectiveness of the online-only CAG intervention, which allows the results to be compared and the added value of blended care to be identified. The blended care format is being added to increase the reach of our intervention, specifically targeting a population that would not access an online-only intervention on their own. The blended care protocol has been developed in cocreation with survivors, GPs, and PNs to ensure the best fit with the general practice context and the needs of survivors ([name], unpublished data, 2025). However, some challenges cannot be foreseen. Conducting the RCT in a period following the global COVID-19 pandemic may place limitations on our study protocol. For example, it may be difficult to achieve our target sample size due to recruitment problems with both GPCs and survivors of cancer. In the aftermath of COVID-19, the health care sector is facing a workforce shortage, partly due to the retirement of a large proportion of the working population [55,56]. In primary care, this is leading to the closure of GPCs as owners are not being replaced by a new generation. Meanwhile, the COVID-19 pandemic has resulted in a high rate of delayed care, further increasing the demand for GPCs and leaving little room for trial participation and research activities such as patient recruitment. This resulted in a difference in the number of GPCs recruited compared to our target. We aimed to recruit 40 GPCs, but in reality, only 26 GPCs were recruited.

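### The second Bayes factor pairs two hypotheses that are both true for any effect between zero and the online-only value, so it is uninformative in that range

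*Protocol article*

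**What the plan says.** The Statistical Methods overview in the protocol article describes a Bayes factor as expressing the "relative strength of the evidence supporting competing hypotheses". Two are planned.

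- **First:** blended care does better than usual care, "as opposed to support for the hypothesis that the conditions do not differ or that the blended CAG intervention has a smaller effect" than usual care. This is d > 0 against d <= 0, and the two sides exclude each other.
- **Second:** the article words it as "the hypothesis that the blended CAG intervention has no smaller effects than care as usual will be compared to the support for the hypothesis". Its opposing side reads: "blended CAG intervention has smaller effects than the effects found in the online-only CAG intervention", with the online-only effects taken from previous research.

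The Sample Size section gives online-only effects on lifestyle behaviours of 0.20-0.40 at 6 months. The Discussion shows what the comparison is for. Principal Findings treats similar results as confirmation that the adapted programme keeps its effectiveness. Strengths and Limitations says that likeness to the previous research "allows the results to be compared and the added value of blended care to be identified". The trial has two arms, blended care and a waiting list, and no online-only arm.

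**The concern.** The two sides of the second Bayes factor use different reference points. One is measured from usual care (zero), the other from the online-only effect. The plan's own figures put the online-only effect above zero, so the hypotheses overlap and do not compete in the sense in which the article defines a Bayes factor.

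The overlap covers the result that matters most here: blended care better than usual care but weaker than the cheaper online-only programme. The second Bayes factor is the only analysis described that brings in the online-only effect. If it is run as written, a value near 1 or slightly above could be read as weak support for blended care keeping its effectiveness, when the same data point the other way.

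**Working it through.** **The regions.** Let d be the standardised effect of blended care against usual care, positive meaning benefit.

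- Hypothesis A, as written: d >= 0.
- Hypothesis B, as written: d < d_online.
- Both true: 0 <= d < d_online. The upper end is 0.20, 0.30 or 0.40 across the range in Sample Size.

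The plan states no figure to reproduce, so the rest shows what the overlap does.

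**Inputs.** From Sample Size: 141 per condition and a design effect of 1.27. Assumed: d_online = 0.30 (midpoint of 0.20-0.40, treated as known) and a normal prior on d centred at 0 with SD 10. The article says only that default priors will be used, so other scales are tried below.

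**Standard error.** SE = sqrt(2/141 x 1.27) = sqrt(0.01801) = 0.134.

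**Formula.** BF(A:B) = (posterior mass of A / prior mass of A) / (posterior mass of B / prior mass of B).

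**Estimate of 0.20.** With this prior the posterior is close to normal, mean 0.20, SD 0.134.

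- Posterior masses: P(d >= 0) = 0.932; P(d < 0.30) = 0.772; both at once, 0.704.
- Prior masses: P(d >= 0) = 0.500; P(d < 0.30) = 0.512.
- As written: (0.932/0.500) / (0.772/0.512) = 1.24.
- Complementary pair, d >= 0.30 versus d < 0.30: (0.228/0.488) / (0.772/0.512) = 0.31, about 3 to 1 for less than online-only.

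**Other estimates, same assumptions.**

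| Estimate | As written | Complementary |
|---|---|---|
| 0.10 | 0.85 | 0.08 |
| 0.15 | 1.02 | 0.16 |
| 0.20 | 1.24 | 0.31 |
| 0.30 | 2.02 | 1.05 |
| 0.40 | 4.5 | 3.5 |
| 0.50 | 15 | 14 |

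Between 0.10 and 0.20 the written factor stays near 1, while the complementary pair moves from about 13 to 1 to about 3 to 1 against blended care matching online-only.

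**Other priors, estimate 0.20.** For prior SD 0.5, 1 and 10, each centred at 0 or at 0.30, the written factor runs from 0.85 to 1.66 and the complementary factor from 0.30 to 0.62. The written factor falls on either side of 1 depending on the prior; the complementary factor stays below 1.

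**More data.** If the true d lies inside the overlap, both posterior masses tend to 1 and the written factor tends to (prior mass of B) / (prior mass of A). For zero-centred priors this is 0.512/0.500 = 1.02 at SD 10 and 0.618/0.500 = 1.24 at SD 1. (The match with the 1.24 above is a coincidence.) The limit reflects the prior alone. The complementary factor tends to 0.

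**Recruitment to date.** The Results section reports 127 participants in 26 practices. Assuming an even split and no dropout, 127/26 = 4.88 per practice, the design effect is 1 + 3.88 x 0.03 = 1.117, and SE = sqrt(2/63.5 x 1.117) = 0.188. At an estimate of 0.20 the factors are 1.25 and 0.44, so the contrast is weaker but has the same pattern.

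**The case against.** **It may be a slip.** Usual care in the first half of the sentence may have been meant as the online-only programme. That one change gives the complementary pair. This is plausible, but no other section defines the pair differently, and an analyst following the text would run the wrong comparison.

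**The factor is not useless.** A Bayes factor for overlapping hypotheses can be computed, and it rises when blended care is clearly above online-only (4.5 at an estimate of 0.40, 15 at 0.50). This stands. The fault is confined to the overlap.

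**Does it favour the wrong side however large the sample?** A reader might infer this. The text does not support it: inside the overlap both hypotheses are true, so neither side is wrong. The factor is uninformative there.

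**Does the prior check bias the result to the null?** The article says "It will be verified that these prior distributions are sufficiently diffuse, do not overwhelm the data, and do not destabilize the analysis". A reader might infer that wide priors turn evidence for an effect into evidence against it. That needs a point null. The article joins no difference with a smaller effect, which is naturally d <= 0. On that reading, with z = 2 and SE 0.213, the factor for an effect rises from 29 at prior SD 0.5 to 43 at SD 10. The same sentence also guards against priors that destabilise the analysis.

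**The comparison is openly external.** The article ties it to previous research and claims no randomised contrast with online-only. This is correct. Only the confidence of the added-value wording is at issue.

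**Conclusion.** The point holds as an error in a stated hypothesis pair. For any effect from 0 up to the online-only value, the second Bayes factor cannot separate keeping the online-only effect from losing part of it, and a larger sample does not help. The overlap follows from the article's own text and its 0.20-0.40 range, with no modelling. The sizes (1.24 against 0.31 at an estimate of 0.20; limits of about 1.0 to 1.24) rest on an assumed d_online of 0.30 treated as known, normal priors and the planned sample size. That the intended question is blended against online-only is inferred from the second half of the sentence and from the Discussion.

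Severity is moderate. The Bayes factors supplement the multilevel regression of blended against usual care, which is untouched, as are the first Bayes factor, the randomisation and the sample size.

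**What to change.** - Restate the second pair as d >= d_online versus d < d_online for each outcome. If the comparison with usual care should stay in the same analysis, use three ordered regions: d < 0, 0 <= d < d_online and d >= d_online.
- State d_online for each outcome and time point. The 0.20-0.40 range covers lifestyle behaviours at 6 months only.
- Carry the uncertainty of the earlier estimate into the comparison instead of treating it as a fixed cut-off.
- Report the result as an indirect, non-randomised comparison, and soften the Strengths and Limitations statement that added value will be identified.

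The cost is rewording and a few extra model runs. The downside is a softer claim about added value. The article expects analysis to start in spring 2025, after data collection, so the pair should be corrected before the data are analysed.
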